## Abstract

**Background:**

Cardiac autonomic neuropathy is a commonly overlooked complication of type 2 diabetes mellitus (T2DM) characterized by an imbalance between sympathetic and parasympathetic supply to the heart, which contributes to cardiovascular morbidity and mortality. T2DM has also been shown to negatively influence oxygen kinetics and increase oxidative stress, which may be linked to the development of various chronic complications. Aerobic training has been reported to improve oxygen uptake, antioxidant defense, and cardiac autonomic function in T2DM; however, the effects of varying doses of exercise on these variables are not known. Therefore, the aim of the present study is to explore the effects of manipulating training variables (volume and intensity) on the regulation of oxygen uptake response, oxidative stress, and cardiac autonomic function in patients with T2DM.

**Methods:**

We will recruit 60 patients with T2DM, who will be randomly allocated into one of the three aerobic training groups: low-intensity, low-volume training; low-intensity, high volume-training; high-intensity, high-volume training; or to the control group receiving no supervised exercise. All participants will be assessed for the rate of oxygen uptake, levels of antioxidant enzymes and cardiac autonomic function at baseline and after 12 weeks of training. Secondary outcome measures will include cardiometabolic risk factors and body composition.

**Discussion:**

Despite a large body of evidence on the efficacy of aerobic training in the prevention and treatment of T2DM, there is no unequivocal exercise prescription for the same. Oxygen kinetics and oxidative stress are highly sensitive to the magnitude of physical activity. It would therefore, be interesting to study their interaction with chronic exposure to various doses of exercises and explore the optimal volume and intensity to bring about improvements in these parameters.

**Trial registration:**

Clinical Trials Registry – India, CTRI2017/08/009459. Registered on 23 August 2017. Retrospectively registered.

**Electronic supplementary material:**

The online version of this article (10.1186/s13063-018-2671-y) contains supplementary material, which is available to authorized users.

## Background

The current worldwide prevalence of diabetes mellitus is 425 million and is projected to reach 628 million by the year 2045 [1], with type 2 diabetes mellitus (T2DM) accounting for at least 90% of the cases [2]. T2DM is associated with dysfunction of various organs especially the heart and peripheral blood vessels, making it a multi-faceted metabolic disorder, with twofold to fourfold higher incidence of cardiovascular disease compared to patients without diabetes mellitus [3]. Diabetes mellitus has been reported to affect oxygen consumption causing a blunting of both peak and dynamic responses of oxygen uptake implying impairment of the control of oxygen delivery to and/or utilization of oxygen by contracting muscles [4]. In addition, hyperglycemia-induced oxidative stress is one of the major focuses of recent research related to diabetes mellitus [5]. Growing evidence indicates that oxidative stress is increased in diabetes mellitus because of the overproduction of reactive oxygen species (ROS) and the decreased efficiency of antioxidant defenses [6–8] and may be linked to the development of chronic complications of diabetes mellitus [9, 10]. Mechanisms that contribute to the formation of free radicals in diabetes mellitus may include not only increased non-enzymatic and auto-oxidative glycosylation, but also metabolic stress resulting from changes in energy metabolism, the levels of inflammatory mediators, and the status of antioxidant defense systems [11, 12]. Another commonly overlooked complication of T2DM, cardiac autonomic neuropathy (CAN) is characterized by an imbalance between the sympathetic and parasympathetic supply to the heart, which contributes to cardiovascular morbidity and mortality [13]. The pathogenesis of diabetic CAN is complex and involves a series of pathways activated by hyperglycemia resulting in increased oxidative stress, which can cause direct neuronal dysfunction or, endothelial dysfunction resulting in neuronal ischemia and cellular death [14].

### Aerobic training in diabetes mellitus

Considering the predominance of an inactive lifestyle in modern-day societies, exercise training constitutes the cornerstone of cardiovascular disease prevention in the diabetic population. Aerobic exercise is known to reduce weight and maintain good glycemic control, and thus reduce the risk of cardiovascular disease among diabetic patients [15]. The beneficial effects of aerobic training on the metabolic profile include significant reductions in indices of obesity (reduction in body mass index (BMI), total fat mass, sum of skin fold measurements, waist circumference and/or waist-to-hip ratio), improved cardiovascular risk profiles (increase in high-density lipoprotein/low-density lipoprotein cholesterol (HDL-C/LDL-C) ratio, normalization of lipid profiles, lowered blood pressure (BP) and resting heart rate, improved cardiac output and oxygen extraction), increase in the (sub)maximal aerobic exercise capacity, a significant decrease in glycemia and significant increase in insulin sensitivity, insulin secretion, and/or reduced glycosylated hemoglobin (HbA1c) concentrations [16–20]. It also improves skeletal muscle capitalization and blood flow, muscular glucose transporter 4 (GLUT4) levels, hexokinase, and glycogen synthase activities [21].

In addition, aerobic training has been shown to improve oxygen uptake kinetic responses [22]. It has also been proven to enhance resting vagal activity and depress the sympathetic outflow [23] and recent reviews have emphasized its role in significant improvement in cardiac autonomic function in T2DM [24, 25]. Furthermore, Oliveira et al. [26] showed that an aerobic training program in subjects with T2DM resulted in important upregulation of antioxidant enzyme levels and increased nitric oxide bioavailability, which may help minimize oxidative stress and the development of the chronic complications of diabetes mellitus. The exercise-induced oxidative stress may function in a manner similar to the general principles of exercise training. That is, in order for an adaptation to occur, the physiological stimulus applied (in this case, ROS and reactive nitrogen species (RNS) production) must exceed a certain minimal threshold, effectively overloading the system. If overload is achieved, the physiological capacity of the body will expand or adapt, ultimately leading to improvement in health and/or human performance [27]. It remains to be elucidated however, what dose (volume and intensity) of aerobic exercise can compensate or even super-compensate for ROS production in patients with T2DM. Figure 1 outlines the proposed mechanisms through which aerobic training might improve oxygen uptake, oxidative stress, and autonomic modulation.

**Fig. 1 Fig1:**
[figure not shown]
Exercise-mediated impact on oxygen uptake, oxidative stress, and cardiac autonomic function. ↓ downregulation/suppression, ↑ upregulation/stimulation, *eNOS* endothelial nitric oxide synthase, *nNOS* neuronal nitric oxide synthase, *iNOS* inducible nitric oxide synthase

### Research objective and hypothesis

Although the American Diabetes Association (ADA) recommends at least 150 min/week of moderate-intensity aerobic physical activity or at least 90 min/week of vigorous aerobic exercise distributed over at least 3 days/week and with no more than 2 days consecutively without physical activity [28], a dose- response relationship with health benefits remains unclear. Therefore, the present study aims to evaluate the dosimetry of aerobic training programs in the regulation of oxygen kinetics, oxidative stress, cardiac autonomic function, and cardiometabolic parameters in T2DM. We hypothesize that varying the volume and intensity of aerobic training will result in a significant difference in oxygen uptake, oxidative stress, and cardiac autonomic function in patients with diabetes mellitus.

## Methods

### Study design

The study is a single-blinded randomized controlled trial (with blinding of the outcome assessor) evaluating the dose response of aerobic training in patients with T2DM. It is a four-arm comparative pretest-posttest experimental design with random allocation of subjects into groups using a lottery method (Fig. 2). This trial has been designed in accordance with the Consolidated Standards of Reporting Trials (CONSORT) statement and is reported as per the Standard Protocol Items: Recommendations for Interventional Trials (SPIRIT) statement (Fig. 3). Additional file 1 shows this in more detail.

**Fig. 2 Fig2:**
[figure not shown]
Flowchart of study design

**Fig. 3 Fig3:**
[figure not shown]
Standard Protocol Items: Recommendations for Interventional Trials (SPIRIT): Specific research plan and implementation steps. *LILV* low-intensity, low-volume training; *LIHV* low-intensity, high-volume training; *HIHV* high-intensity, high-volume training

The study is approved by the Institutional Ethical Committee, Jamia Millia Islamia, New Delhi, India. All participants will be given an information sheet explaining the study purpose, methodology and their rights as research subjects. Written consent will be obtained.

### Participants

We will recruit 60 patients with T2DM from the university health center and nearby hospitals. Consenting participants will be randomly allocated into one of the three aerobic training groups: low-intensity, low-volume training (LILV); low-intensity, high volume-training (LIHV); high-intensity, high-volume training (HIHV), or to the control group receiving counselling and dietary advice but no supervised exercise. The inclusion and exclusion criteria are listed in Table 1.

**Table 1 Tab1:** Inclusion and exclusion criteria for patient recruitment

Inclusion criteria	Age 30–70 years
	Diagnosis of type 2 diabetes mellitus ≥ 12 months
	Glycosylated hemoglobin (HbA1c) level 6.5–10%
	Receiving oral anti-diabetic medication
	Able to walk continuously for at least 20 min and climb one flight of stairs unaided without stopping
	Sedentary: do not engage in exercising more than 20 min on 3 or more days a week
Exclusion criteria	Body mass index > 40 kg/m^2^
	Exogenous insulin
	Autoimmune diseases
	Retinopathy, nephropathy, peripheral neuropathy
	Inflammatory and other conditions potentially associated with altered cytokine regulation
	Liver impairment
	Renal insufficiency (creatinine levels > 2.0 mg/dl)
	Diagnosed cardiovascular disease; recent onset of cardiac-origin symptoms
	Prescription of a very low caloric diet (fewer than 1000 kcal/day) or drugs for the treatment of obesity
	Orthopedic problems limiting physical activity
	Already engaging in intensive physical activity for > 2 h/week

### Recruitment method

The treating physician will screen (all) potential participants from the outpatient department of the Ansari Health Centre, Jamia Millia Islamia and inform them about the study. Potential participants interested in participating in the study will be referred to the Diabetes Rehabilitation Clinic where they will receive the participant information sheet and those meeting the inclusion criteria will be invited to participate in the trial. If they agree to participate, they will be required to sign a consent form and baseline data will be collected.

### Group allocation

Random allocation to one of the four groups will occur after confirmation of eligibility and baseline assessment. Blind allocation by a remote researcher will be performed using computer-generated random numbers. The concealment of allocation will be ensured by using sequentially numbered, sealed, and opaque envelopes.

### Procedures

Subjects with T2DM will be recruited based upon the inclusion and exclusion criteria and will be informed about the study. After explaining the purpose and methodology, participants will be given a consent form explaining their rights as research subjects. Following screening for eligibility, all participants will be required to visit the center on three separate days. Before each test, the subjects will be given a thorough demonstration. On the first day of testing, blood samples will be collected, and subjects will be assessed for body composition, resting blood pressure, and heart rate variability. On the second day of testing, the subjects will report to the Human Performance Laboratory, Centre for Physiotherapy and Rehabilitation Sciences (CPRS) where they will perform the graded maximal test and on day 3, they will perform the 20-min submaximal test (at 50% volume of oxygen consumed (VO_2_max)) to examine oxygen kinetics. After baseline testing, they will be allocated into one of the three aerobic training programs: low-intensity, low-volume training (LILV); low-intensity, high-volume training (LIHV); high-intensity, high-volume training (HIHV), or to the control group receiving counseling and dietary advice but no supervised exercise. All identifying information on the consent form and demographic/history questionnaire will be kept confidential by assigning a number to each subject.

### Interventions

Herein, VO_2_Reserve (VO_2_R) = VO_2_max – VO_2_rest, calculated during the graded maximal test for each subject. Participants will be randomly allocated into one of the four groups:i.Low-intensity, low-volume training (LILV) 3 times/week performing treadmill walking at 50% VO_2_Rii.Low-intensity, high-volume training (LIHV) 5 times/week performing treadmill walking at 50% VO_2_Riii.High-intensity, high-volume training (HIHV) 5 times/week performing treadmill walking at 80% VO_2_Riv.Control group receiving counseling and dietary advice but no supervised exercise.

### Outcomes

The primary and secondary outcomes are listed in Table 2. All outcomes will be assessed at baseline and after 12 weeks of intervention.

**Table 2 Tab2:** Outcomes and criterion measures

Primary Outcomes	
Oxygen Uptake Response	
a) Maximal Response	Peak oxygen consumption
b) Dynamic Response	Time constant of rise to steady state (“on” kinetics) Time constant of recovery from steady state (“off” kinetics)
Oxidative stress	
a) Antioxidant enzymes	Catalase Superoxide dismutase Glutathione peroxidase
b) Reactive species	Nitric oxide
Cardiac Autonomic Function	
a) Resting	Heart Rate Variability Time-domain indices: AvgNN, SDNN, RMSSD, pNN50 Frequency-domain indices: Total power, LF, HF, LF: HF ratio
b) Post-exercise	Heart rate recovery at 1 (HRR_1min_) and 2 min (HRR_2min_)
Secondary Outcomes	
Cardiometabolic risk factors	
a) Glycemic control	Glycosylated hemoglobin Fasting blood glucose
b) Lipid profile	Total cholesterol High-density Lipoprotein Low-density Lipoprotein Triglycerides
c) Resting blood pressure	Systolic blood pressure Diastolic blood pressure
Body composition	
a) Body fat (%)	Percent body fat derived from sum of skinfolds
b) Central obesity	Waist circumference Waist-Hip ratio

*AvgNN* Mean of N-N intervals, *SDNN* Standard deviation of N-N intervals, *RMSSD* Square root of the mean squared differences between adjacent RR intervals, *pNN50* Percentage of interval differences of adjacent RR intervals greater than 50 milliseconds derived from differences between consecutive RR intervals, *LF* Low frequency power, *HF* High frequency power, *LF/HF ratio* Ratio of low and high frequency power

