#### Sample size calculation

The number of subjects was determined using Software G. Power 3.192. An effect size of 0.44 was obtained from the data relative to changes in maximum aerobic capacity in a study by Lambers et al. [38], which examined the effects of aerobic training on obesity and cardiovascular risk in T2DM. A priori analysis of sample size using the *F* test (repeated measures analysis of variance (ANOVA), within-between interaction) showed that the total sample size required would be 52 to have 95% power at effect size of 0.44 and alpha level of 0.05. Considering the dropout rate from a previous similar investigation [30], the total sample size obtained is 60 or 15 subjects per group, using the allocation ratio of 1 for the four groups.

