#### Statistical analyses

The intention-to-treat (ITT) analysis set will include all subjects who were randomized to the study and received at least one session of training. The normality of distribution will be examined for all variables and those found to have a non-normal distribution will be log transformed for further analyses. One-way ANOVA will be used to compare the groups at baseline. To test for the differences between groups and across two assessments, 4 × 2 split-plot ANOVA with group (LILV, LIHV, HIHV, control), time (baseline, 12 weeks) and interaction effect (Group × Time) will be employed. If the main effect of a group is found to be significant, the Bonferroni test will be employed as post hoc analysis. The significance level will be set at *p* < 0.05.

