### Ethics

The trial methodology has been designed to incorporate features that minimize bias in controlled trials: randomization, concealed allocation, specification of eligibility criteria, blinded outcome assessment, blinded analysis, and ITT analysis.

This protocol was registered at the Clinical Trials Registry of India (CTRI/2017/08/009459) and was prospectively approved by the Institutional Ethical Committee, Jamia Millia Islamia (Reference:17/9/43/JMI/IEC/2015).

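### The analysis is called ITT, but the only between-group test named uses only people with both visits, so anyone without a 12-week value is dropped and the result is a complete-case analysis

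*Protocol article*

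**What the plan says.** Four statements in the protocol article bear on this.

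- **Label.** The Ethics section names among its bias-limiting features "blinded outcome assessment, blinded analysis, and ITT analysis".
- **Analysis set.** Under Statistical analyses: "The intention-to-treat (ITT) analysis set will include all subjects who were randomized to the study and received at least one session of training". A trained participant who attends one session and leaves later belongs to this set.
- **Test.** The same paragraph names one between-group analysis: "4 × 2 split-plot ANOVA with group (LILV, LIHV, HIHV, control), time (baseline, 12 weeks"), with the group-by-time interaction.
- **Visits.** Under Outcomes: "All outcomes will be assessed at baseline and after 12 weeks of intervention". The abstract words the time point as "cardiac autonomic function at baseline and after 12 weeks of training". There is no intermediate visit.

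On numbers, the Sample size calculation says that "the total sample size required would be 52 to have 95% power at effect size of 0.44 and alpha level of 0.05", and then: "Considering the dropout rate from a previous similar investigation [30], the total sample size obtained is 60 or 15 subjects per group". The dropout rate itself is not printed.

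**The concern.** The set and the test do not fit together. The set includes people who leave after starting; the test has no place for anyone whose second value is missing. With two time points, a classical split-plot ANOVA tests the interaction through each person's change, and a person without a 12-week value has no change to contribute. Such people are in the ITT set on paper and absent from the result.

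This is a different defect from the session rule inside the ITT definition. That rule has its own difficulty: read literally, it shuts out the control group, which gets no supervised exercise. But if it were deleted and all 60 randomised people were in the set, the ANOVA would still remove everyone without a 12-week value.

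What is at stake is the comparison of doses. The arms ask for very different effort, so loss could plausibly differ between them and be related to exercise tolerance. Peak oxygen consumption, a primary outcome, is closely tied to tolerance. The Discussion hopes to identify the best volume and intensity, and unequal selective loss can distort exactly that ranking.

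**Working it through.** **1. Reproduce the plan's sample size.** Inputs from the Sample size calculation: f = 0.44, alpha = 0.05, power 95%, k = 4 groups, repeated-measures within-between interaction. The m = 2 measurements come from Statistical analyses. The correlation rho between visits is not given. Using the noncentral F test:

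- lambda = f² × N × m / (1 − rho), df1 = (k − 1)(m − 1) = 3, df2 = (N − k)(m − 1) = N − 4.
- With rho = 0, the smallest N is 49, which rounds up to 52 for four equal groups. Power at 52 is 0.964. This matches the plan.
- With rho = 0.5 the answer would be 28, which does not match.

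So 52 is the number of people with both visits on which the stated power rests.

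**2. Implied loss.** 60 − 52 = 8 people, and 8/60 = 13.3%. By division, 52/(1 − 0.133) = 60. Multiplying 52 by 1.15 gives 59.8, which also rounds to 60, so the rate in the cited study could be somewhat different. Either way the allowance is 8 people.

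**3. Planned burden by arm** (Interventions section, 12 weeks): control 0 supervised sessions; LILV 3 × 12 = 36; LIHV 5 × 12 = 60; HIHV 5 × 12 = 60, at 80% rather than 50% of VO2 reserve.

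**4. How large could the distortion be?** The documents give no loss rates by arm and no outcomes for people who leave. The following are illustrations on assumed inputs, not estimates. Assume that those missing gained nothing and that the control arm does not change.

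- All 8 losses in the training arms: 8/45 = 17.8%. The complete-case effect is 1/(1 − 0.178) = 1.22 times the as-randomised effect.
- 4 of 15 lost in HIHV and 1 of 15 in LIHV, with equal gain d in those assessed: complete cases show no difference between the arms. As randomised, the gains are 11/15 = 0.73d and 14/15 = 0.93d.
- If those missing gained as much as those assessed, there is no distortion.

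**5. Power if everyone were assessed.** Same zero-gain assumption, rho = 0, loss at the same rate d in each training arm, unchanged variability; the effect size becomes 0.44 × (1 − d).

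| Loss d | Complete cases | Power, complete cases at f = 0.44 | Diluted f | Power, all 60 |
|---|---|---|---|---|
| 10% | 54 | 0.970 | 0.396 | 0.954 |
| 13.3% | 52 | 0.964 | 0.381 | 0.938 |
| 20% | 48 | 0.948 | 0.352 | 0.893 |
| 30% | 42 | 0.910 | 0.308 | 0.788 |

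At the implied loss, analysing everyone would cost little power even under this pessimistic assumption.

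**The case against.** The strongest objection concerns a reading that the wording invites: that the follow-up visit is reserved for people who finish the programme, so that everyone who stops training is dropped and the trial compares completers. The text does not support this. The abstract's sentence has all participants as its subject. Controls attend the same visit although they never train, so for them the phrase can only mean a calendar point. Statistical analyses labels the second time point simply as 12 weeks. Someone who stops in week 5 and attends in week 12 would be analysed. This objection stands in full.

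Second, raising 52 to 60 is a routine allowance for loss to follow-up, and trials that follow everyone make it too. This also stands: it shows that missing values are expected, not that stopping training means leaving the study.

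Third, rules for missing data and for follow-up after stopping may lie in a full protocol or SAP that is not shown, and their absence from an article is no fault. That is right, and the point does not rest on absence. The article itself fixes the set, the test and the visits and calls the result ITT, and those fixed elements do not agree. An imputation rule elsewhere could repair the mismatch, but the test as named here does not.

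Fourth, a mixed model is only a partial cure. With two visits, a person with baseline only contributes no observed change, and the model in effect predicts the missing value from people in the same arm with a similar baseline. If those who leave gain nothing, most of the 1.22-fold inflation in the illustration would remain. This stands, and is why the fix also needs actual 12-week data and a sensitivity analysis.

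**Conclusion.** The point holds in limited form. The named ANOVA does not deliver the ITT property that the article claims; it gives a complete-case result, with about 8 of 60 (13%) expected to be missing on the plan's own allowance. This follows from the stated set, test and visits, provided that no imputation rule exists elsewhere.

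A bias in the dose ranking is a risk, not a demonstrated result. Its size and direction cannot be computed from the documents; the figures 1.22 and 0.73d against 0.93d rest on assumed splits and zero gain in those missing. It is tempting to add that the most demanding arm would be favoured, but the documents give nothing by arm to establish that. The visit wording is loose enough to need tightening, but it does not exclude people who stop training. This deserves correction before results are called ITT; it does not by itself invalidate the design.

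**What to change.** - **Abstract (Methods) and Outcomes:** state that outcomes are assessed 12 weeks after randomisation for every randomised participant, whether or not training continued. The article reports recruitment from February 2016 with an expected end in May 2018, so this can apply only to participants not yet past that point.
- **Statistical analyses, main analysis:** analyse all randomised participants by allocated arm, using a likelihood-based mixed model that retains those with baseline only. State its assumption: loss is explained by baseline value and arm.
- **Statistical analyses, sensitivity:** add an analysis that gives training-arm participants with a missing 12-week value the control-arm change.
- **Label:** if the split-plot ANOVA on complete pairs is kept, call it a complete-case analysis.

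The cost is an amendment, for which the article already describes a route through the ethics committee, and a little more analysis work. The visits are already planned. Some who stop training will decline to attend, and the as-randomised effect may be somewhat smaller than the complete-case effect.

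### Seventeen variables are designated primary and tested at an unadjusted 0.05, while the stated 95% power refers to only one of them

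*Protocol article*

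**What the plan says.** All references are to the protocol article.

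- **Outcomes, Table 2.** The primary block covers three domains. Oxygen uptake has peak oxygen consumption and the on and off time constants. Oxidative stress has three enzymes ("Catalase Superoxide dismutase Glutathione peroxidase") and nitric oxide. Cardiac autonomic function has eight resting indices ("Time-domain indices: AvgNN, SDNN, RMSSD, pNN50 Frequency-domain indices: Total power, LF, HF, LF: HF ratio") and heart rate recovery at 1 and 2 minutes. No variable is placed above the others.
- **Statistical analyses.** A 4 × 2 split-plot ANOVA (group, time, interaction) is the stated model. One threshold covers everything: "The significance level will be set at *p* < 0.05". The only adjustment is a Bonferroni post hoc test, which follows a significant group effect.
- **Sample size calculation.** "An effect size of 0.44 was obtained from the data relative to changes in maximum aerobic capacity". The test is the within-between interaction at alpha 0.05 with 95% power. It gives 52 subjects in total, raised to 60 for dropout.

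**The concern.** Calling a variable primary means that a significant result on it carries the trial's main claim. With 17 such variables, each at 0.05, the trial gives itself 17 chances of a significant primary result. The Bonferroni step does not help, because it compares arms after one variable has already given a significant group effect and does nothing across variables.

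The power statement has the same weakness. It is calculated for one variable at a full, unshared alpha of 0.05. The other 16 have no stated power, and 95% would no longer hold at this sample size if alpha were shared among all 17.

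What is at stake is how a reader should weigh an isolated significant enzyme or heart rate variability index reported as a primary result.

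**Working it through.** **1. Count of primary variables (Table 2).** Peak oxygen consumption 1, time constants 2, enzymes 3, nitric oxide 1, heart rate variability 8 (4 time-domain and 4 frequency-domain), heart rate recovery 2. Total: 1 + 2 + 3 + 1 + 8 + 2 = 17.

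**2. The plan's own figure.** Inputs from the sample size section are f = 0.44, alpha = 0.05, k = 4 groups and m = 2 assessments. The pre-post correlation ρ is not stated. For the within-between interaction:

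- λ = f² · N · m / (1 − ρ), df1 = (k − 1)(m − 1) = 3, df2 = (N − k)(m − 1).
- With ρ = 0 and N = 48: λ = 0.1936 × 48 × 2 = 18.59, df2 = 44, power 0.948.
- With ρ = 0 and N = 52: λ = 0.1936 × 52 × 2 = 20.13, df2 = 48, power 0.964.

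So 52 is the first multiple of four to reach 95%, and the stated figure is reproduced at ρ = 0. Going from 52 to 60 implies about 13.3% dropout (1 − 52/60).

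**3. Error rate across the 17, if training affects none of them.** One interaction test per variable at 0.05.

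- Independent variables: 1 − 0.95^17 = 0.582.
- Expected number of false positives, whatever the correlation: 17 × 0.05 = 0.85.

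The article gives no correlations between variables, so the following are assumptions. With two time points the interaction test equals a one-way ANOVA on change, which was simulated for 4 × 15 subjects with 20,000 replicates.

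| Assumed correlation among the 17 changes | Chance of at least one significant interaction |
|---|---|
| 0.3 within blocks of related variables, 0 between | 0.55 |
| 0.7 within blocks, 0 between | 0.45 |
| 0.7 to 0.9 among the eight heart rate variability indices only | 0.50 to 0.45 |
| 0.8 within blocks, 0.3 elsewhere | 0.39 |
| 0.3 between all pairs | 0.51 |
| 0.5 between all pairs | 0.41 |
| 0.7 between all pairs | 0.29 |
| 0.9 between all pairs (extreme) | 0.16 |

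A simpler simulation with equally correlated normal test statistics gives 0.49, 0.39 and 0.27 at common correlations 0.3, 0.5 and 0.7. Together these give the working range of 27–55%.

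**4. What each remedy does to the sample size (f = 0.44, ρ = 0).**

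| Primary outcomes | Alpha at strictest step | Power at N = 52 | Power at N = 60 | Evaluable N for 95% |
|---|---|---|---|---|
| One | 0.05 | 0.964 | 0.984 | 52 |
| One per domain, Holm over three | 0.05/3 = 0.0167 | 0.908 | 0.952 | 60 |
| All 17, Bonferroni | 0.05/17 = 0.0029 | 0.754 | 0.849 | 76 |

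**The case against.** **The null is unlikely to hold everywhere.** The background section cites training benefits on oxygen uptake, antioxidant enzymes and autonomic function, and the sample size itself assumes an effect on aerobic capacity. Each real effect removes an opportunity for a false positive. This stands. A reader might infer that a false primary finding is simply about as likely as not, but the documents do not support that without conditions. It needs no effect on any variable and modest correlation between them.

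**Several variables are linked by construction.** LF:HF is computed from LF and HF, RMSSD and pNN50 both come from adjacent intervals, and the two recovery values subtract from the same peak heart rate. This also stands, and it is why a range is given. Even a common correlation of 0.7 leaves the rate at 27–29%.

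**The hypothesis is worded conjunctively.** The research objective expects differences in oxygen uptake, oxidative stress and autonomic function together. A reader might infer that one significant variable out of 17 is enough to declare success. The article states no such rule, so that reading cannot be attributed to the plan.

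**The trial is exploratory, and the analysis plan may settle the matter.** The abstract does speak of exploring, and a success rule may properly sit in a plan that is not shown, so its absence here is not the point. The point is what the article does state: 17 variables labelled primary, one unadjusted level, a hypothesis of significant differences, and 95% power for one variable. Basing a sample size on one variable is not in itself an error; here that variable shares primary status with 16 others.

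**Group and time tests.** One might add these to the count. A time effect is not a false training finding, because every arm, including the counselled control group, may change over 12 weeks. Only the interaction is counted above.

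**Conclusion.** The point holds in conditional form. The plan as written designates 17 primary variables at an unadjusted 0.05 and supplies power for one. If training affected none of them, the chance of at least one significant primary interaction would be about 58% under independence and roughly 27–55% under the assumed correlations. It would be lower if some effects are real. Uniform correlation of 0.9, implausible across three physiological domains, would still give about 16%, three times the nominal level.

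The count, the single threshold and the basis of the sample size come directly from the article. The correlations are assumptions, and the power figures rest on the pre-post correlation of 0 that reproduces 52. The fault concerns which results may carry a confirmatory claim; it does not affect randomisation, data collection or the effect estimates.

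**What to change.** Before outcome data are analysed, and through the route in the Protocol amendments section (ethics committee approval, then notice to the registry):

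1. Name "Peak oxygen consumption", the Table 2 measure of the capacity on which the sample size rests, as the single primary outcome at 0.05. The 52 evaluable and 60 recruited then stand as calculated.
2. Make the other 16 variables secondary, reported with confidence intervals and Holm-adjusted within each domain.

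**Cost.** No extra patients or measurements are needed. Claims on oxygen kinetics, oxidative stress and autonomic function become secondary. Recruitment began in February 2016 and registration was retrospective, so the late change of outcome status must be disclosed, with its date and reason, when results are reported.

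**Alternative.** If all three domains must stay primary, nominate one variable in each, apply Holm across the three, and restate the power. On the article's inputs with pre-post correlation 0, it is about 91% at 52 evaluable at the strictest step. Reaching 95% needs 60 evaluable, which is the whole planned sample with no dropout.
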